**Fig. 1 Fig1:**
[figure not shown]
Development of the ‘Get Healthy!’ program. The project steering committee members invited to provide feedback were [name], [name], [name], [name], [name], [name], [name], [name], [name], Assoc. [name], [name], [name] and [name]. Additionally, nutrition and exercise physiology student researchers [name], [name], [name], [name], [name], [name], [name] and [name] contributed to the program design

A summary of physical activity and nutrition content, and session structure, as well as required equipment, is provided in Table 1. Participants in the ‘Get Healthy!’ program engage in a minimum of three contact hours each week, for a continuous 12-week period. Contact hours are made up of two 1-h physical activity sessions, held on non-consecutive days, and 1 h per week of guided nutrition information and support. In order to decrease participant time and transportation burden, we will run the weekly nutrition session immediately before or after one of the exercise sessions. Participants will therefore only need to attend the program on two out of 7 days per week. The physical activity component of the program is delivered by an accredited exercise physiologist, and the nutrition-related component of the program is delivered by an Accredited Practicing Dietitian. Both of these program leaders have previous experience running interventions for people with intellectual disability. Intervention intensity and advice is tailored to the individual needs of each participant; however, the program is ideally delivered in a small group setting (three to six people per group). The program can be run in a number of settings; however, access to specialised exercise and monitoring equipment is required for pre- and post-testing as well as some of the physical activity sessions*.* In order to support sustained behaviour change post-intervention, the exercise physiologist will also provide examples throughout the program of accessible and low-cost ways to increase physical activity without specialised equipment.

**Table 1 Tab1:** ‘Get healthy!’ curriculum content

Component	Time commitment	Topics	Resources required^a^

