### Study population

Inclusion/exclusion criteria: Participants with mild to moderate intellectual disability and their carers will be recruited into the study. Level of ID will be determined based on the report of referring disability agencies or primary caregivers. In order to test the feasibility of the ‘Get Healthy!’ program for older adults with ID, participants aged 40 years and over will be preferentially recruited. Participants deemed to be at extreme psychiatric, behavioural or physical health risk, and participants with an insufficient range of motion to participate in the physical activity component of the program will be excluded from the study. Full inclusion and exclusion criteria for both the person with ID and carer groups are outlined in Fig. 2.

Sample size: As this is primarily a feasibility study, it is not powered to demonstrate statistical significance. Between 8 and 10 adults with intellectual disability and carers in total will be recruited using convenience sampling. This sample size and recruitment methodology is based on the research teams’ previous recruiting experience with this difficult to access population. Limiting the study sample size will also allow us to engage with each participant’s progress in a detailed fashion. We will seek comprehensive feedback from each individual in order to refine the program for future use.

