### Feasibility outcomes

Participation rates: Individual participation in each week’s nutrition session and each physical activity sessions will be scored:0 = Did not attend1 = Attended but only participated minimally. For example, attempted < 50% of activities, did not join in group discussions2 = Attended and participated moderately well to very well. For example, engaged in > 50% of activities, was part of group discussions.

At the completion of the intervention these scores will be totalled and participants will be categorised into high (100–75% score), medium (50–74% score) or low (< 50% score) participation groups for the purposes of analysis.

Drop-out rates and reasons: Drop-out rates and reasons will be recorded to help determine the acceptability of the program to participants.

Acceptability of data collection measures and procedures: The distribution of missing data within each measure will help to determine the acceptability of measures to program participants. Exit interviews will also be conducted with all participants to capture qualitative data on the acceptability of the program and data collection measures for individual participants. Exit interview schedules have been designed with accessible language to enable participation. All interviewers will have had previous experience leading interviews or focus groups with people with ID.

Adverse outcomes: Participants who develop any physical injury or other emerging health issue during the trial will be referred back to their GP for review and clearance prior to continuing. Participants displaying psychological distress will be referred to relevant mental health support services. All adverse physical and psychological outcomes will be recorded and reported in subsequent publications.

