Benchmark results indicating a definitive larger scale trial may be feasible will include the following:Drop-out rate of < 70%A majority of participants (> 60%) achieving ‘high’ or ‘medium’ participation scoresPositive qualitative feedback from > 80% of participants regarding their experience of undertaking the programThe feasibility of each individual outcome measure will be assessed separately. If less than half of participants were able to complete the outcome measure the research team will review in detail reasons for failure to implement the measure. Based on this review, we will either modify how the measure is implemented in the larger trial (for example, providing participants with additional prompts and support to complete a measure), or replace the outcome measure if it appears impractical to implement in our target population.

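### The drop-out benchmark of under 70% is met when 5 of 8 or 6 of 10 participants are lost, so it barely discriminates and sits badly with the other feasibility thresholds

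*Protocol article*

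**What the plan says.** The Outcome measures section makes the feasibility indicators the primary outcomes of the pilot. Under Feasibility outcomes, drop-out is one of them: "Drop-out rates and reasons will be recorded to help determine the acceptability of the program to participants".

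The same section introduces its thresholds with "Benchmark results indicating a definitive larger scale trial may be feasible will include the following". The first is "Drop-out rate of < 70" (per cent). The others are more than 60% of participants with a high or medium participation score, and positive qualitative feedback from more than 80%. Each outcome measure is then judged separately: "If less than half of participants were able to complete the outcome measure the research team will review in detail reasons".

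Participants are "categorised into high (100–75% score), medium (50–74% score) or low (< 50% score) participation groups". On feedback, "Exit interviews will also be conducted with all participants".

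The sample is given under Study population: "Between 8 and 10 adults with intellectual disability and carers in total will be recruited using convenience sampling".

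The article gives no reason for 70%. It also does not say whether all benchmarks must be met, or whether the percentages are taken over everyone enrolled or over completers.

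**The concern.** A feasibility benchmark should be hard to meet when a program is not acceptable to the people it is meant for. This one tolerates losing most of a very small sample over a 12-week program. The benchmarks beside it ask for clear majorities to take part and to be positive, so a reader would expect the drop-out limit to be of similar strictness.

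At stake is the reading of a primary outcome. The pilot could report its drop-out benchmark as met with three or four people left, and that result would be cited in support of a larger trial. The 70% is a stated number, so this is not a detail left to a fuller document.

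**Working it through.** There is no derivation of 70% to reproduce. The check is a count of whole participants plus an exact binomial calculation.

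**Inputs.** n = 8, 9 or 10 (Study population). Thresholds: drop-out < 70%, participation > 60%, feedback > 80%, and a review trigger below one half (Feasibility outcomes). Scored sessions: "Contact hours are made up of two 1-h physical activity sessions, held on non-consecutive days, and 1 h per week of guided nutrition" (Background to the program), each scored 0 to 2.

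**Step 1: counts.** Largest d with d/n < 0.70, and smallest k with k/n > 0.60 or k/n > 0.80, all enrolled as denominator.

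| n | Most lost | Completers | Participation needs | Feedback needs |
|---|---|---|---|---|
| 8 | 5 (62.5%) | 3 | 5 | 7 |
| 9 | 6 (66.7%) | 3 | 6 | 8 |
| 10 | 6 (60.0%) | 4 | 7 | 9 |

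**Step 2: chance of meeting the drop-out benchmark.** P(X ≤ d) with X ~ Binomial(n, p), where p is an assumed true drop-out.

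| True drop-out | n = 8 (d = 5) | n = 9 (d = 6) | n = 10 (d = 6) |
|---|---|---|---|
| 50% | 0.855 | 0.910 | 0.828 |
| 60% | 0.685 | 0.768 | 0.618 |
| 80% | 0.20 | 0.26 | 0.12 |

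**Step 3: can all three benchmarks pass at the largest tolerated loss?**

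- *All enrolled.* At n = 10 with 6 lost, even if all 4 completers succeed, 7 − 4 = 3 drop-outs must score medium or better and 9 − 4 = 5 must give positive feedback. The maximum score is 12 × 3 × 2 = 72. Leaving after week 6 with full marks gives 36/72 = 50% (medium); after week 9, 54/72 = 75% (high). So this is possible, but only with late, well-attended departures and interviews of people who left. If no drop-out could qualify, the other two benchmarks would cap losses at 10 − 7 = 3 and 10 − 9 = 1.
- *Completers only.* At n = 10 with 4 completers, 3 of 4 (75%) and 4 of 4 (100%) meet the other two. All three benchmarks pass with 60% of the sample lost.

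**Step 4: the one-half review trigger.** If people who leave are not measured afterwards, at most 3/8 = 37.5%, 3/9 = 33.3% or 4/10 = 40% can complete any week-13 assessment. All are below one half. At exactly 50% lost (4 of 8, 5 of 10) the trigger is not reached.

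**Step 5: drop-out < 30% for comparison.** The most that may be lost is 2 at each n (25.0%, 22.2%, 20.0%). P(X ≤ 2) at true drop-out of 50% is 37/256 = 0.14, 46/512 = 0.09 and 56/1024 = 0.05. At an assumed true drop-out of 20% it is 0.80, 0.74 and 0.68 (for n = 10: 0.107 + 0.268 + 0.302).

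**The case against.** The strongest reply is that this is one of three descriptive benchmarks in a pilot of 8 to 10 people. The text says only that the benchmarks indicate a larger trial may be feasible, and sets no formal stop or go rule. Drop-out rates and reasons will be recorded in any case, so readers can judge the observed rate. The benchmark also does fail more often when drop-out is extreme: at a true 80% it passes with probability of only 0.12 to 0.26. All of this stands and limits the consequence, but none of it explains 70%.

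Three stronger readings are tempting, and the document does not support them:

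- *The thresholds contradict each other.* They measure different things and can all be met together, as the week-6 leaver with 36 of 72 points shows.
- *Every week-13 measure would fail.* The one-half rule prompts a review followed by modification or replacement, not a failure. It names no time point: the clinical measures are also taken at baseline, and weight, waist, blood pressure and ergometer fitness at week 6 (Table 2). It bites only above 50% loss, and only if leavers are not measured.
- *The program would be judged feasible after losing 6 of 10.* That is true of this one line. The overall judgement depends on a combination rule and denominators that the article does not state.

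**Conclusion.** The point holds as one about a lax, unexplained and mismatched threshold. The benchmark is met with 5 of 8, 6 of 9 or 6 of 10 lost. If true drop-out were 60%, it would be met more often than not (0.685, 0.768, 0.618), so it barely discriminates as an acceptability criterion. On one reading of the denominators all three benchmarks can pass with 60% lost; on the other the drop-out line is almost redundant. It can also read as met while every week-13 assessment falls below the review trigger.

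The probabilities assume independent drop-out with a common rate, and the 50% and 60% rates are illustrations, since the article does not define an unacceptable rate. If carers count towards the 8 to 10, as the Study population wording suggests, completers with intellectual disability could be fewer than shown. A reader might infer that the authors meant retention above 70%. That is plausible, but nothing in the document confirms it.

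**What to change.** 1. State the intended figure. If retention was meant, write the benchmark as retention to week 13 of more than 70% of all enrolled participants, that is, drop-out below 30% and at most 2 lost at n = 8, 9 or 10. Keep the inequality strict or say otherwise: at n = 10, allowing exactly 30% admits a third loss and raises the pass probability at 50% true drop-out from 0.05 to 0.17.
2. If another figure was meant, give it with a reason, and set it no higher than 50% so that it agrees with the one-half review trigger.
3. Take all three benchmarks over everyone enrolled, and say whether all must be met and how people who leave are scored and interviewed.
4. Report the observed drop-out with an exact 95% confidence interval.

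The cost is a few lines of text and a benchmark that is harder to meet. Under the 30% version, a program with a true drop-out of 20% would still miss it about 20% to 32% of the time (1 − 0.80 at n = 8, 1 − 0.68 at n = 10), which is a reason to present it with the interval and not as a verdict by itself.

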### Clinical outcomes

Body mass index (BMI) will be calculated using the formula BMI = weight/height (kg/m^2^). Participants will be weighed to the nearest 100 g. Height in metres will be measured to the nearest 1 mm. All participants will be requested to remove their shoes and heavy jackets/overcoats prior to data collection.

Waist circumference (WC) will be measured at the midpoint between the iliac crest and the lowest rib, in full expiration, to the nearest 0.1 cm while the person is standing.

Cardiovascular fitness (CV fitness) will be assessed using the YMCA sub-maximal ergometre test (12 min duration): number of minutes/stages performed, peak HR (% of APMHR), peak workload achieved and predicted VO_2_ peak (ml/kg/min) if appropriate.

Physical strength will be measured using 30-s modified push up test, medicine ball throw/chest pass, 10RM strength testing and 30 s Sit to Stand test.

Blood pressure will be measured using a sphygmomanometre while the participant is seated and has rested for least 5 min prior to data collection. Blood pressure is taken in both the right and left arms. Forearm will be placed at mid-sternal level during the procedure.

Engagement in physical activity (PA) and amount of sedentary behaviour (SB): *Objective PA and SB data* will be collected using a waist-based GTX3 actigraph accelerometre worn for a period of 5 days in each data collection period. Participants will be encouraged to wear the actigraph at all times during these days, apart from when they shower. Information about steps, and percentage of sedentary behaviour and light, moderate-vigorous PA will be collected.

In order to make our results comparable with earlier studies in adult ID populations, we will use the actigraph protocol outlined in Harris et al. [44] that involves the following:A minimum requirement of at least 6 h of data on at least three of the five wear daysAccelerometres to record activity over 15-s intervals, with activity counts of four consecutive epochs summed to give activity counts per minute (cpm). Four categories of activity intensity defined for data analysis:• Sedentary behaviour 0–499 cpm• Light intensity activity 500–1951 cpm• Moderate intensity activity 1952–5724 cpm• Vigorous intensity activity greater than 5725 cpmThe accelerometre data will then be used to calculate the mean time (minutes) and the percentage time per day, spent in each level of activity.

Detailed information about the validity and reliability of objective measurements of physical activity and sedentary behaviour in adults with ID are lacking. However, actigraph accelerometres are the most commonly used objective measurement tool in the adult ID literature to date. At least nine previous studies with adults with ID [33, 34, 37, 44–49] have used this methodology, either alone or in combination with subjective measures. The majority of these studies used a sedentary behaviour cut-off point of < 500 counts per minute in view of recent findings that adults with ID spend more energy when engaged in sedentary activities than the general population [50, 51].

*Subjective PA and sedentary behaviour data* will be collected using the International Physical Activity Questionnaire-proxy respondent (IPAQ-pr) proxy report [52]. Information will be collected from a carer with input from the participant with ID where possible. The purpose of the subjective questionnaire is to elicit more detailed information about the types of PA and sedentary behaviours the person is engaged in. For participants who are unable to tolerate the actigraph, this questionnaire may also provide a useful approximation of changes in PA and SB levels across the intervention. In cases where both measures are successfully collected, we will link the actigraph and IPAQ-pr data to explore concurrence of findings across measures.

The original IPAQ measure was a 7-day self-report recall questionnaire and was not developed for people with ID. This instrument has good psychometric properties [51]. The IPAQ-pr see [52] changed the original IPAQ from a 7-day recall questionnaire to an activity diary to be completed by carers. The IPAQ-pr was found to be a reliable and valid measure for categorising whether participants with ID met recommendations for physical activity levels when completed by a parent or support staff of the adult with ID [52].

Dietary intake (energy intake, food group consumption and diet quality) will be measured using the following:Three-day photographic food record and a proxy-assisted 24-h recall, interpreted and analysed by two Accredited Practicing Dietitians using Foodworks® (version 9) nutrition analysis software (Xyris Software, 2018) and cross checked for inter-rater reliability.Calculation of Healthy Eating Index for Australian Adults (HEIFA) to measure diet quality, conducted by at least one Accredited Practising Dietitian.

The 3-day photographic food record is a validated method for assessment of food intake in adults with ID [32, 53–55]. The 3-day photographic food record method was compared to direct observation by an investigator in 18 adults with ID over a 1-day period with an intra-class correlation of 0.84, *p* < 0.001 [54]. This method was selected as studies suggest a 3-day weighed food record (WFR) may be impractical for people with ID due to cognitive impairments and difficulty in measuring portion sizes. Proxy-assisted food records may also be impractical with studies reporting inaccurate measurements and reduced fidelity when burden is placed on the carer for data collection. A 3-day digital photography gives participants independence and allows food consumed away from carer to be easily captured [54]. Reminder messages will be provided by investigators to maximise compliance. The Accredited Practising Dietitians will clarify photographic records with participants and parents/carers prior to analysis, utilising a food checklist to minimise foods missed from the photographic food record.

Foodworks® nutritional analysis program (version 9) provides a comprehensive breakdown of energy, macro- and micronutrient, fat subgroups, added sugar, fibre and food group intakes. Data from this program will be entered into a pre-developed Microsoft Excel spread sheet to calculate the Healthy Eating Index for Australian Adults (HEIFA-2013) score. The HEIFA-2013 is a singular score based how close dietary intake is to the current Australian Dietary Guidelines [56]. The tool is validated in young adults 18–34 years. The tool has not been validated in older adults or ID population. To our knowledge, diet quality has not been previously studied in older adults with ID, and therefore, this study could provide a unique set of data. A study in Queensland, Australia, is applying a 4-day WFR and the HEIFA to assess the diet quality of individuals with a disability undergoing a sporting intervention (unpublished data).

Nutrition and physical activity knowledge will be assessed using the Nutrition and Activity Knowledge Scale for Use with People with an Intellectual Disability (NAKS) questionnaire. This questionnaire has been reported to have good psychometric properties in adults with ID. For detailed information about the validity and reliability of this measures see Illingworth et al. [57]. Previous studies examining nutrition and physical activity knowledge in populations with ID have also reported successfully using this measure [58–60].

Quality of life will be measured using the Personal Wellbeing Index - Intellectual Disability (PWI-ID) [61]. This index is administered to the person as an interview and covers the following domains: standard of living, health, life achievement, personal relationships, community-connectedness and future security. The adult version of the measure has been reported to have good reliability and validity when used with adults with ID [62].

Data analysis plan: Quantitative data will be analysed using the Statistical Package for Social Science (SPSS). Given the small sample size, primary analysis will focus on descriptive statistics and confidence interval estimations for outcomes of interest. While this trial is not powered to detect statistically significant differences, we will use paired *t* tests in an exploratory fashion to analyse normally distributed continuous variable data collected at two timepoints only (baseline and 13 weeks). The nonparametric Wilcoxon signed-rank test will be used in cases where data are not normally distributed. To explore any group effects of the intervention when there are two timepoints, we will calculate the difference between completion and baseline timepoints for each measure and then compare the mean of the differences using *t* tests. Regression modelling adjusting for clustering will be used to analyse data collected at three or more timepoints. Appropriate imputative techniques will be used to account for any missing data points where appropriate. We will also analyse the impact of gender on feasibility and clinical outcomes. This analysis will be exploratory in nature in view of the small sample size. Qualitative data collected from exit interviews will be digitally recorded and transcribed verbatim. Transcribed data will be thematically analysed to identify program strengths, weaknesses, suggestions for improvement, and overall perceived impact. The software program NVivo (version 11.0.0) will be used to support organisation of qualitative data.

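### The dietitians who code the food photographs also clarify them with participants first, so coding is probably not masked to timepoint, and the inter-rater check would not reveal a shared bias

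*Protocol article*

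**What the plan says.** All references are to the protocol article.

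- **Who analyses.** Under Clinical outcomes, the photographic record and the 24-h recall are "interpreted and analysed by two Accredited Practicing Dietitians using Foodworks® (version 9) nutrition analysis software", and the results are "cross checked for inter-rater reliability".
- **Who clarifies.** Later in the same section: "The Accredited Practising Dietitians will clarify photographic records with participants and parents/carers prior to analysis, utilising a food checklist". The stated purpose of the checklist is to reduce missed foods. The sentence is not limited to one timepoint.
- **Diet quality.** The HEIFA calculation is "conducted by at least one Accredited Practising Dietitian". It is computed from the nutrition software's output: "Data from this program will be entered into a pre-developed Microsoft Excel spread sheet to calculate the Healthy Eating Index".
- **When.** Table 2 marks dietary intake at week 0 and week 13 only.
- **Who delivers the program.** In the background section on the program, "the nutrition-related component of the program is delivered by an Accredited Practicing Dietitian". The article does not say whether this person is one of the two analysts.
- **Design and status.** There is one intervention group and no comparator (Design). Clinical outcomes are secondary and exploratory (Outcome measures). The data analysis plan relies on descriptive statistics, confidence intervals and exploratory paired tests.

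**The concern.** Identifying foods and estimating portions from photographs takes judgement. A dietitian who has just gone through a record with the participant or carer will usually know whether it was made before or after a 12-week program. If the same dietitian then codes it, what he or she expects of the program can influence the coding. With no control group, any coding difference between baseline and week 13 is counted as change. The cross-check between raters looks like a safeguard, but it measures agreement, not freedom from an expectation that both raters hold.

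What is at stake is how the exploratory diet changes can be interpreted, and whether a coding procedure open to this bias is carried into the larger trial that the pilot is meant to inform.

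**Working it through.** The plan gives no figure to reproduce, so the check sets the statements side by side and follows their consequence.

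**1. Are clarifiers and coders the same people?** The analysis sentence introduces two dietitians ("interpreted and analysed by two Accredited Practicing Dietitians"). The clarification sentence then refers back to the dietitians with a definite article ("The Accredited Practising Dietitians will clarify photographic records with participants and parents/carers prior to analysis"). The natural reading is that the same two people do both. This follows from a stated procedure, not from silence about blinding.

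**2. Would they know the timepoint?** Table 2 places the records at weeks 0 and 13, before and after the 12 weeks of sessions. A conversation about a record at either point would normally make the timepoint plain. This step is an inference from Table 2 and the unqualified clarification sentence: likely, but not stated.

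**3. What does that do to the estimate?** For participant *i*, let *T* be true intake and *b* the coding bias at each timepoint:

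- recorded change = (*T*13 + *b*13) − (*T*0 + *b*0) = true change + (*b*13 − *b*0).

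A bias that is equal at both timepoints cancels. A bias that depends on knowing the timepoint does not; it moves the mean change by the average of (*b*13 − *b*0). If it is the same for everyone, the confidence interval shifts without widening, and a paired *t* test or signed-rank test cannot separate it from true change.

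**4. Would the cross-check show it?** On one record, rater A minus rater B reflects *b*A − *b*B. If both hold the same expectation to a similar degree, this is near zero and agreement looks good. The check would show a bias only to the extent that the raters differ in it.

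**5. Does the HEIFA spreadsheet protect the score?** It removes judgement from the arithmetic, not from the coding that feeds it. A coding bias therefore passes into HEIFA, for which only one dietitian is required.

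**6. What can be sized?** The bias cannot: the article gives no portion-estimation error, standard deviation or expected diet change. The coding workload can. With 8 to 10 people in total and one photographic record each at two timepoints, there are 8 × 2 = 16 to 10 × 2 = 20 records. There would be fewer if carers counted in the total supply none, or if records are missing.

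**7. Does masking address it?** A coder who does not know the timepoint applies, in expectation, the same *b* to both records, so (*b*13 − *b*0) is about zero for rater expectation. Changes in what participants choose to photograph or report belong to the record itself and remain.

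**The case against.** The strongest case against has four parts.

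- **No decision rests on diet change.** The benchmarks under Feasibility outcomes concern drop-out, participation, participant feedback and whether enough people could complete each measure. Coding bias alters none of these. This stands and limits the weight of the point.
- **A condensed article may omit coding order and de-identification.** Clarifying before analysis is compatible with annotating at collection and coding later without dates. That is fair as far as it goes, but removing dates would not mask someone who has already discussed the record, and the article does assign both tasks to the same dietitians.
- **Other aids narrow the room for judgement.** The checklist, the standard software and the pre-built spreadsheet do help. None of them masks the coder.
- **Unmasked measurement is common in single-group pilots.** True, but here coding from photographs can be separated in time and person from contact with the participant.

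A reader might also infer more than the document supports:

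- *That the dietitian who taught the sessions scores the records.* The article neither says nor excludes this.
- *That the bias favours the program.* The direction is not shown. A checklist for missed foods tends to add intake back, which could work the other way.
- *That the size is known.* One could say that coding portions 5% smaller at week 13, on an assumed 2000 kcal/day, gives 0.05 × 2000 = 100 kcal/day of spurious change. Both inputs are assumptions, and the result is not an estimate for this study.
- *That the 24-h recall is equally affected.* The clarification sentence covers photographic records only.

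**Conclusion.** The point holds as a modest weakness of design. As written, the dietitians who analyse the 3-day photographic records have already clarified them with participants and carers, and so are likely to know which timepoint they are coding. In a single-arm study, rater expectation could enter the exploratory pre-post change in energy, food groups and HEIFA, and the inter-rater cross-check would not reveal a bias that both raters share.

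Size and direction cannot be derived from the document. The primary feasibility outcomes are unaffected. The conclusion rests on two readings: that the clarifying dietitians are the two analysts, and that clarification takes place at both weeks 0 and 13. It does not depend on either of them having delivered the sessions. It is worth acting on because the change is cheap and the pilot is meant to settle measurement procedures for a larger trial.

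**What to change.** Keep clarification, which serves completeness, and separate it from the coding that produces the results:

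1. One of the two planned dietitians clarifies and annotates each photographic record at collection, using the same checklist script at baseline and week 13. The annotations should not mention the timepoint or the program.
2. After week 13, all records are stripped of date and identity, put in random order and coded in one batch by the other dietitian, who did not clarify them and preferably did not deliver the sessions.
3. The masked coder's entries are used for the pre-post diet results and for HEIFA. The first dietitian's coding is kept only for the inter-rater check.
4. The report states that masked coding does not remove participants' own desirable reporting after nutrition teaching.

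**Cost.** Relabelling and shuffling about 16 to 20 records, and holding the coding for the results until the program ends. Both coding roles are filled by the two dietitians already planned.

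**Downsides.** Queries that arise during late coding, especially about baseline meals, are harder to resolve with participants and carers, so annotation at collection must be thorough. Some photographs may still hint at the timepoint. If one of the two dietitians delivered the sessions, that person would be the clarifier, which leaves the desirable-reporting limitation in place.
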